## Design

The study design is a parallel-group randomised trial with 12 week follow-up (see Figure 1), comparing two interventions: commercially available rocker-sole footwear (MBT® Matwa, Masai Barefoot Technology, Switzerland) *versus* prefabricated foot orthoses (Vasyli Customs, Vasyli Medical™, Queensland, Australia). The study has been designed using the principles described by Osteoarthritis Research Society International Clinical Trials Task Force guidelines [40]. Permuted block randomisation with random block sizes, stratified by sex, will be undertaken using an interactive voice response telephone service provided by the NHMRC Clinical Trials Centre at the University of Sydney, New South Wales, Australia to ensure allocation concealment. Participants will be informed that they will receive either the rocker-sole footwear or the foot orthoses (i.e. they will not be blinded to their group allocation). Due to the nature of the intervention, research staff administering the treatments cannot be blinded to group allocation. However, follow-up assessment of outcome measures will be via self-completion questionnaires returned by mail, and those entering outcome measure data and conducting statistical analyses will be blinded.

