### Sample size

The sample size for the study has been determined using an *a priori* power analysis based on the primary outcome measure: the pain domain of the FHSQ [73]. We have previously determined that the minimal important difference for this measure in people with foot pain is 13 points [79]. Using a standard deviation of 19 (derived from our recent trial [17]), a power level of 0.8, alpha level of 0.05 and accounting for a drop-out rate of 15%, a sample size of 80 participants (i.e. approximately 40 per group) will be required. We have conservatively ignored the extra precision provided by covariate analysis when estimating the sample size, and have conservatively selected a drop-out rate at the higher end of previous trials of specialised footwear and/or orthoses for lower limb OA (between 2 and 15%) [30,80-82].

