### Statistical analysis

Statistical analysis will be undertaken using SPSS® version 21.0 (IBM Corp, NY, USA) using the intention-to-treat principle for all randomised participants [38]. The exception to this will be the safety outcome measures which will be analysed as treated. In participants with bilateral symptoms, the most painful foot will be analysed. Multiple imputation will be used to replace any missing data using five iterations, with age, baseline scores, and group allocation as predictors [83]. The exception will be for the variables use of rescue medication and co-interventions where no data substitution will be applied. Standard tests to assess continuous data for normal distribution will be used and transformation carried out if required. Differences in the primary and secondary outcome measures between the two groups will be compared. Continuously-scored outcome measures will be analysed using analysis of covariance with baseline scores and intervention group entered as independent variables [84]. Ordinal scaled data will be analysed using non-parametric tests. Dichotomously-scored outcome measures will be compared using relative risk, risk difference and number needed to treat. For the gait analysis component of the study, differences in biomechanical variables will be compared using paired *t*-tests and effect sizes (or in the case of non-normally distributed data, medians will be compared using Mann–Whitney U tests).

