A third, related issue is that because we will openly disclose the two treatments during the recruitment process, there is some risk of “resentful demoralisation” in participants who are allocated to the prefabricated foot orthoses group. That is, some participants who are allocated to receive the prefabricated foot orthoses may be resentful of not receiving the more expensive and (more visually substantial) rocker-soled shoe intervention, which may affect their adherence to the tasks required of them in the study and systematically influence their responses to the outcome measure questionnaires [58]. To address this, we will document both participant preference prior to randomisation and participants’ perceptions of treatment credibility/expectation after randomisation. This approach will not *prevent* resentful demoralisation, but will enable post-randomisation effects of treatment preference to be quantified, and if necessary, factored into the analysis as a prognostic variable.

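### Randomisation is stratified by sex, but the fixed ANCOVA and imputation lists omit it: a minor and conditional loss of precision that one added covariate removes

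*Protocol article*

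**What the plan says.** Under Design, the protocol article states the allocation method: "Permuted block randomisation with random block sizes, stratified by sex, will be undertaken". No other stratification factor is named.

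Under Statistical analysis, one model is fixed for every continuous outcome, including the primary: "Continuously-scored outcome measures will be analysed using analysis of covariance with baseline scores and intervention group entered as independent variables". Missing values are multiply imputed "with age, baseline scores, and group allocation as predictors". Sex is in neither list, although Baseline assessments records it as a demographic factor.

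The only other covariate mentioned anywhere is treatment preference, which the Discussion says may, if needed, be "factored into the analysis as a prognostic variable".

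Under Sample size, the plan says that "the minimal important difference for this measure in people with foot pain is 13 points", takes a standard deviation of 19, and states that precision gained from covariates was left out of the calculation.

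**The concern.** Blocking within sex makes the arms nearly equal in sex mix. Whatever sex contributes to outcome then largely cancels from the treatment contrast, so the true sampling variance of the estimate falls. An ANCOVA without sex does not see this: the between-sex variance stays in its residual, and the reported standard error exceeds the true one. Confidence intervals are then wider than they need to be, and the test rejects less often than 5% under the null.

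The analysis would fail to use a feature that the design put in on purpose. At stake is precision, not bias. The article gives two explicit predictor lists and does not defer covariates to another document, so this is a choice it has made.

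**Working it through.** **Inputs from the protocol article.** Difference 13 points, SD 19, power 0.80, alpha 0.05, drop-out 15%, total 80 (Sample size); stratification by sex (Design); model and imputation lists (Statistical analysis).

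**Assumptions, because the document gives no figure.** Two-sided test; 65% women; baseline-outcome correlation 0 or 0.5; difference g between the sexes in baseline-adjusted 12-week pain of 0, 5, 10 or 13 points; total SD held at 19.

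**1. The plan's own figure.** n per arm = 2 × (1.960 + 0.842)² × (19/13)² = 33.5, rounded up to 34. Then 34/0.85 = 40 per arm, 80 in total. The stated size reproduces from a two-sample formula with no covariates.

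**2. Share of residual variance due to sex.** R² = 0.65 × 0.35 × g² / [19² × (1 − ρ²)]. The model without sex has a standard error larger by the factor 1/√(1 − R²). Example, g = 13 and ρ = 0.5: 0.2275 × 169 / 270.75 = 0.142, and 1/√0.858 = 1.080.

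**3. Power at 34 completers per arm.** With ρ = 0 and no sex term, SE = 19 × √(2/34) = 4.608, and power = Φ(13/4.608 − 1.96) = Φ(0.861) = 80.5%. With ρ = 0.5, SE = 4.608 × √0.75 = 3.991 and power is 90.3%. Adding sex divides the SE by the factor from step 2.

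| g (points) | ρ = 0: SE excess | ρ = 0: power without → with sex | ρ = 0.5: SE excess | ρ = 0.5: power without → with sex |
|---|---|---|---|---|
| 0 | 0% | 80.5% → 80.5% | 0% | 90.3% → 90.3% |
| 5 | 0.8% | 80.5% → 81.2% | 1.1% | 90.3% → 90.9% |
| 10 | 3.3% | 80.5% → 83.0% | 4.5% | 90.3% → 92.6% |
| 13 | 5.8% | 80.5% → 84.7% | 8.0% | 90.3% → 94.0% |

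An equal split of the sexes moves the largest SE excess only from 8.0% to 8.9%.

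**4. Simulation.** 5,000 trials per setting, 80 participants, blocks of 2, 4 or 6 within sex (assumed sizes), 15% random drop-out, complete-case ANCOVA, ρ = 0.5.

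| g (points) | Type I error without / with sex | Power without / with sex |
|---|---|---|
| 0 | 5.1% / 5.0% | 88.3% / 88.3% |
| 5 | 4.2% / 4.4% | 89.2% / 89.6% |
| 10 | 4.6% / 5.2% | 89.7% / 91.1% |
| 13 | 3.8% / 4.9% | 89.8% / 92.7% |

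At g = 13 the model without sex reports a mean SE of about 4.02 against an empirical 3.76; with sex the two agree (3.72 against 3.71 to 3.73). The Monte Carlo error of a 5% rate is √(0.05 × 0.95/5000) = 0.3 points. The 4.2% at g = 5 is mostly noise, since the model with sex shows 4.4% there. With ρ = 0 and g = 13, power is 79.9% without sex and 83.3% with it.

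**5. Why the simulated gain is smaller than in step 3.** Step 3 takes the model SE as the true one. Stratification has already lowered the true sampling variance, so the unadjusted test does a little better than its own SE implies. For g = 13 and ρ = 0: (13 − 1.96 × 4.608)/(4.608/1.058) = 0.911, a power of 81.9% rather than 80.5%. The differences in step 3 are therefore upper figures.

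**The case against.** The strongest reply is that nothing in the document shows that sex matters for this outcome. The Background links sex to how common the condition is, not to pain at 12 weeks. A sex difference already visible in baseline pain is at least partly absorbed by the baseline covariate. A reader might infer that the standard error simply is too large; the document does not support that without the condition. This part of the reply stands.

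A reader might also infer that power the trial was counting on is being lost, or that it has no reserve. That does not follow. The sample size was computed without any covariate gain, and step 1 confirms it. With total SD 19, the model without sex still delivers the planned level, and the baseline covariate adds to it. What is forgone is an extra.

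Larger effects can be produced, but only with strong inputs. A sex effect of 0.8 SD, a baseline correlation of 0.4 and equal sexes give √[(0.84 + 0.16)/0.84] = 1.09, an SE 9% too large. That effect is 0.8 × 19 = 15.2 points, above the 13-point minimal important difference. It also treats 19 as the within-sex SD, so the total SD becomes 19 × √1.16 = 20.5, not the 19 that the plan uses.

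Finally, the imputation part has not been quantified. At 15% drop-out the effect of omitting sex there should be small unless sex predicts both missingness and outcome, which nothing in the document suggests.

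What the reply does not remove is the mismatch itself: the sole stratification factor is absent from two explicit lists, one of which includes age, which was not stratified on.

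**Conclusion.** The point holds in a limited, conditional form and is minor. The stated analysis does not follow the randomisation. If sex predicts 12-week FHSQ pain given baseline, the SE from the stated model is about 0 to 8% too large and the power forgone is at most about 4 percentage points, over assumed sex differences of 0 to 13 points. For differences up to 5 points the loss is under one point.

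The direction is conservative. The estimate is unbiased, type I error does not exceed 5%, and neither the planned 80% power nor the sample size of 80 changes. The figures rest on the assumed sex split, baseline correlation, sex effect, two-sided test and random drop-out listed above.

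**What to change.** In Statistical analysis, state the model for the primary and all continuous secondary outcomes as *baseline score, intervention group and sex (stratification factor)*. Add sex to the imputation predictors, so that the imputation model contains every variable in the analysis model.

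The cost is one phrase in each of two sentences and one residual degree of freedom out of 80 − 3 = 77. Sex is already recorded, so no new data are needed and the sample size stays the same. Stating this before outcome data are seen also avoids a later, data-driven choice of covariates.

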#### *Biomechanical evaluation*

Because the proposed mechanism of action of the rocker-sole shoes is a change in biomechanical function of the lower limb, two approaches will be used to evaluate their effects at the baseline appointment. First, spatio-temporal parameters and three-dimensional motion of the thigh and lower leg during gait will be recorded using a wireless, wearable sensor motion analysis system (LEGSys™, Biosensics, Boston, MA, USA). This system consists of accelerometers and gyroscopes attached with Velcro™ straps to each lower leg and thigh. The method for calculation of the spatio-temporal parameters of gait is described in detail elsewhere [64]. To summarise, the gait phases are determined from the precise events of heel-strike (initial foot contact) until toe-off (terminal foot contact). These events are extracted from gyroscopes attached to each shank through a local minimal peak detection scheme. Based on each participant’s height and using a biomechanical model, spatial parameters (i.e. stride length and stride velocity) and kinematics (knee and hip) are estimated by integration of the angular rate of rotation of the thigh and shank relative to the waist sensor. Gait analysis with this system has been validated in healthy controls [64], older people [65], and patients with hip osteoarthritis [66]. After a familiarisation period, participants will complete 4 walking trials for each footwear condition over an 8 metre distance. To exclude the effect of acceleration and deceleration steps, only the middle four steps from each trial will be included for analysis. An average recording will be determined from the 16 steps (4 steps from 4 trials) for each condition. Second, plantar pressures (specifically, peak pressure under the hallux, first MTPJ and lesser MTPJs) will be measured with the in-shoe Pedar® system (Novel GmbH, Munich, Germany), a reliable, valid and accurate measure of in-shoe pressure [67-69]. The Pedar® insoles are approximately 2 mm thick and consist of 99 capacitive pressure sensors, arranged in grid alignment. Plantar pressure data will be sampled at a frequency of 50 Hz. Both groups will undergo the same biomechanical assessment. However, for rocker-sole shoe group, comparisons will be made between their own shoes and the rocker-sole shoes, while in the prefabricated foot orthoses group, comparisons will be made when wearing their own shoes (with and without the prefabricated orthoses).

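### The fallback test for non-normal gait and plantar pressure data is an independent-samples test, although every planned comparison is within the same participant

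*Protocol article*

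**What the plan says.** The Biomechanical evaluation section sets up two contrasts, one per arm. In the footwear arm, "for rocker-sole shoe group, comparisons will be made between their own shoes and the rocker-sole shoes". In the orthoses arm, "comparisons will be made when wearing their own shoes (with and without the prefabricated orthoses". The gait data are reduced to one value per person per condition: "An average recording will be determined from the 16 steps (4 steps from 4 trials) for each condition". Each participant therefore contributes a matched pair on each gait variable. Plantar pressures follow the same two-condition comparison.

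The Statistical analysis section recognises this at first: "For the gait analysis component of the study, differences in biomechanical variables will be compared using paired" *t*-tests, with effect sizes. The parenthesis that follows gives the alternative: "in the case of non-normally distributed data, medians will be compared using Mann–Whitney U tests". Earlier in the same section there is a general rule for continuous data: "Standard tests to assess continuous data for normal distribution will be used and transformation carried out if required".

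The article names no paired non-parametric test and describes no comparison of biomechanical variables between the two randomised groups.

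**The concern.** Whether a variable is normally distributed has no bearing on whether its two measurements come from the same person. The sentence changes the assumed design, from paired to independent, because of the shape of the data.

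Mann–Whitney U takes its reference distribution from two unrelated samples. When the samples are the same people measured twice and the measurements are positively correlated, differences between people stay in the noise against which the effect is judged. The test then rejects too rarely under the null and, for modest shifts, too rarely under the alternative.

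At stake is the mechanistic part of the trial. The Discussion relies on it to show how far the interventions reduce hallux pressure and alter lower limb motion, and describes existing evidence on how orthoses work as equivocal. A test tilted towards no change could add an uninformative null result. It would also put paired and unpaired tests side by side in one results table.

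**Working it through.** **Number of pairs.** The Sample size section gives a difference of 13, SD 19, power 0.80, alpha 0.05 (two-sided assumed) and 15% drop-out. Then n per arm = 2 × (1.96 + 0.842)² × 19² / 13² = 33.5, rounded up to 34, and 34 / 0.85 = 40. This reproduces the stated figure: "a sample size of 80 participants (i.e. approximately 40 per group) will be required". The biomechanical data are collected at baseline, so about 40 pairs per arm is reasonable.

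**Assumptions.** The article gives neither a within-person correlation (ρ) nor an expected shift (d, in SD units). Both are varied below.

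**Approximation with normal data, using means.** An independent-samples test takes the standard error of the difference to be √(2/n) = √(2/40) = 0.224 SD. With pairing, the true standard error is √(2(1−ρ)/n). The unpaired statistic therefore has mean d/0.224 and SD √(1−ρ), not SD 1.

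- Type I error is 2 × [1 − Φ(1.96/√(1−ρ))]. At ρ = 0.3 it is 2 × [1 − Φ(2.34)] = 1.9%. At ρ = 0.5 it is 2 × [1 − Φ(2.77)] = 0.6%. At ρ = 0.8 the cut-off is 4.38, and the error is practically zero.
- Unpaired power at d = 0.3, where the mean is 1.34: at ρ = 0.5, Φ((1.34 − 1.96)/0.707) = 19%; at ρ = 0.8, Φ((1.34 − 1.96)/0.447) = 8%.
- Paired power at d = 0.3: at ρ = 0.5, the mean is 0.3 × √40 / √(2 × 0.5) = 1.90 and power is Φ(1.90 − 1.96) = 47%. At ρ = 0.8, the mean is 0.3 × √40 / √(2 × 0.2) = 3.00 and power is Φ(1.04) = 85%.
- The unpaired statistic reaches 1.96 on average at d = 1.96 × 0.224 = 0.44. Below that shift, rising correlation lowers unpaired power; above it, rising correlation raises it. This is why small shifts are the ones at risk.

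**Simulation of the rank tests** (40 pairs, two-sided 0.05; each cell is Mann–Whitney / signed-rank):

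| Data | d | ρ = 0 | ρ = 0.5 | ρ = 0.8 |
|---|---|---|---|---|
| Normal | 0.3 | 25% / 25% | 18% / 45% | 10% / 82% |
| Log-normal, shift on log scale | 0.3 | 26% / 24% | 18% / 43% | about 10% / 80% |
| Log-normal, additive shift | 0.3 | 37% / 31% | 34% / 55% | 29% / 89% |
| Normal | 0.5 | 57% / 57% | 60% / 85% | 65% / near 100% |
| Log-normal, additive shift | 0.5 | 77% / 68% | 85% / 92% | 92% / near 100% |

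Heavy-tailed data, which a log transform would not repair, gave about 34% / 94% at d = 0.3 and ρ = 0.8. That figure depends on the form of the tails and is approximate. Across the distributions tried at d = 0.3, the ranges are 18–34% against 42–64% at ρ = 0.5, and about 10–34% against 80–94% at ρ = 0.8.

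Simulated type I error of Mann–Whitney at a nominal 5% was about 2% at ρ = 0.3, just under 1% at ρ = 0.5 and near zero at ρ = 0.8. The signed-rank test stayed at 4–5%.

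**The case against.** The best defence is that the fallback may rarely be used. The section provides for transformation, and on a plain reading this comes before any non-parametric test. Log-normal data would become normal on the log scale and go to the planned paired *t*-test, so the log-normal rows overstate the practical loss. That argument stands. It does not cover variables that no simple transformation normalises, and the heavy-tailed result shows a similar loss there.

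Second, the loss depends on correlation and effect size, and the article gives neither. With no correlation there is no loss, and Mann–Whitney is slightly ahead in the additive log-normal case (37% against 31%). At 0.5 SD it often still detects the shift. This also stands. However, measurements on the same person in one session would be expected to correlate positively.

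Third, a reader might infer that real biomechanical effects would be hidden, or that the error threatens the trial's conclusions. The article supports neither reading. The first is too categorical, for the two reasons above. The second fails because biomechanical variables are not among the listed primary or secondary outcomes, and continuous outcomes such as FHSQ pain are analysed by analysis of covariance. With positive correlation the error is also conservative, so it does not produce false claims of benefit. The effect sizes planned with the paired *t*-tests help those analyses, but none is named for the fallback.

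Finally, this may be only a misnamed test. Even so, the text names a specific test that does not fit the design, and nothing else in the article corrects it.

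**Conclusion.** Wrong as written; a minor to moderate correction. The mismatch between the fallback and the paired design is plain from the text and needs no assumption. Its size does need assumptions: positive within-person correlation, about 40 pairs per arm, and variables that remain non-normal after any transformation. Under those conditions Mann–Whitney is conservative and could miss shifts of around 0.3 SD that a paired rank test would have a fair to good chance of detecting. At 0.5 SD the disadvantage is smaller, though it does not vanish. The statement that can be defended is that the fallback could miss small to moderate changes, not that it will. Only the mechanistic component is affected.

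**What to change.** In the Statistical analysis section, replace the Mann–Whitney U tests for biomechanical variables with Wilcoxon signed-rank tests on the within-participant differences. State that normality will be judged on those differences. The article does not say otherwise, so this second part is a clarification rather than a correction. A sign test on the paired differences would also respect the design. Reporting a Hodges–Lehmann estimate of the paired difference with a 95% confidence interval is useful but optional.

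The cost is one sentence. No new data, extra participants or change to the primary analysis is needed. If the pairing turned out to carry no correlation, the loss from using the signed-rank test would be nil to modest, as the ρ = 0 column shows.

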## Discussion

The objective of this trial is to compare the effectiveness of rocker-sole footwear and individualised prefabricated foot orthoses in reducing pain associated with OA of the first MTPJ. This will be the third clinical trial undertaken for this condition and the first to focus on footwear-related interventions. Our recent systematic review of interventions for first MTPJ OA [15] revealed only one low quality randomised trial evaluating the effectiveness of two different physical therapy programs in 20 participants [16], and more recently, our group completed an RCT which found that intra-articular viscosupplementation (hylan G-F20) was no more effective than a placebo (sterile saline) [17]. As such, the trial will provide novel and clinically relevant information to inform the non-surgical management of this common and disabling condition.

The underlying biomechanical rationale for the use of mechanical interventions for first MTPJ OA is that the condition results from the inability of the first metatarsal to plantarflex during propulsion to allow the proximal phalanx to dorsally rotate on the first metatarsal head, thereby resulting in dorsal joint compression of the first MTPJ [12,31]. However, the two interventions to be compared in this trial aim to address this biomechanical deficit in different ways. Rocker-sole footwear is thought to reduce the need for first MTPJ dorsiflexion during propulsion, by enabling the body’s centre of mass to “rollover” the base of support, thereby decreasing sagittal plane motion of the ankle [19-22], forefoot [19] and first MTPJ [24], and reducing forefoot plantar pressures [22,23]. In contrast, foot orthoses with a first ray cut-out, forefoot extension and medial wedging aim to limit rearfoot pronation and facilitate first ray plantarflexion during propulsion, thereby allowing the proximal phalanx to rotate on the first metatarsal head to achieve sufficient first MTPJ dorsiflexion [31]. The available evidence addressing this proposed mechanism of action of foot orthoses, however, is equivocal. While two studies have reported increases in first MTPJ dorsiflexion with orthoses placed under the foot in static stance [85,86], one study reported no change in first MTPJ dorsiflexion [87]. Gait studies have been similarly inconsistent, with two studies reporting a *decrease* in first MTPJ dorsiflexion (with medial wedging [88] and orthoses [34]) and one study reporting no change [35].

The prefabricated orthoses in this study will be modified in a similar manner to the protocol described by Welsh *et al*. [35]. However, there are two key differences in the inclusion criteria between our two studies. In the Welsh *et al*. study, participants were excluded if they had an FPI score <4 or exhibited less than 40 degrees of non-weightbearing first MTPJ dorsiflexion. This approach is based on three assumptions: (i) that people with first MTPJ OA are more likely to have pronated feet; (ii) that control of rearfoot pronation is an important goal of treatment for this condition, and; (iii) that individuals with less than 40 degrees of non-weightbearing first MTPJ dorsiflexion would not benefit from the orthoses. Participants in our trial will not be excluded on the basis of foot posture, as our recent systematic review did not find pronated foot posture to be strongly associated with this condition [12]. Furthermore, the gait analysis component of the Welsh *et al*. study found no differences in rearfoot motion with the orthoses, suggesting that control of rearfoot pronation did not contribute to the observed improvement in symptoms. Finally, participants in our trial will be required to have less than 64 degrees of first MTPJ dorsiflexion (as we have shown that this cut-off is associated with radiographic OA in the first MTPJ [41]), but we will not exclude any participants on the basis of having insufficient range of motion in the first MTPJ. It could be argued that individuals with very limited first MTPJ range of motion have little to gain from prefabricated foot orthoses with a modification (a first ray cut-out) that, theoretically, facilitates motion at the first MTPJ by allowing the first ray to plantarflex. However, this mechanism is yet to be adequately demonstrated, and it is possible that the orthoses could achieve beneficial therapeutic effects through other mechanisms, such as reducing peak pressure under the hallux and first MTPJ [85].

The gait analysis component of the study will provide useful insights into the possible mechanism of action of the interventions. The wearable sensor motion analysis system (LEGSys™, Biosensics, Boston, MA, USA) provides high resolution temporal and kinematic data, without the laboratory constraints and data processing requirements of traditional motion analysis systems [89]. The use of this system will help identify changes in lower limb function associated with the footwear and orthoses (particularly changes in sagittal plane motion of the shank and thigh), and whether these changes are related to improvement in symptoms. Similarly, the in-shoe plantar pressure system (Pedar®, Novel GmbH, Munich, Germany) will identify the extent to which the high peak pressures under the hallux frequently observed in individuals with first MTPJ OA [6,90] are mitigated by the interventions. It should be noted, however, that it is not possible to measure first MTPJ motion *directly* in this study, as this requires the permanent modification of the upper of the shoe to allow placement of reflective markers or electromagnetic motion sensors on the foot.

Participants will be reviewed at 4-weekly intervals up to 12 weeks, which is similar to previous footwear trials which have employed 8 week [91] or 12 week [29,30,92] follow-up periods, and longer than the 4 week physical therapy trial for first MTPJ OA by Shamus *et al*. [16]. Although our trial of viscosupplementation for first MTPJ OA followed participants for 24 weeks, the effect of treatment clearly plateaued at 12 weeks in both groups [17]. We are therefore confident that the 12 week duration of the trial is sufficient to detect differences between the groups, if they exist. Furthermore, 12 weeks is considered to be a standard clinical follow-up period in trials evaluating the effects of interventions for OA [70]. The trial will incorporate 4 repeated measurements for the primary outcome measure (baseline, 4 weeks, 8 weeks and 12 weeks) to provide insights into the trajectory of any improvements in symptoms. However, to address the issue of multiple testing of serial measurements [71,72], we have pre-specified 12 weeks as the primary end-point, and no statistical comparisons of the 4 and 8 week scores will be undertaken.

There are three key limitations of the study design. Firstly, this is not a *controlled* trial, as both groups will receive an active intervention that has the potential to be therapeutically beneficial. This was an ethical requirement of our institution, as our original proposal to include “sham” orthoses as the comparator [63] was considered by the ethics committee to be withholding “usual” care. Because usual care is not well documented for this condition, we selected what we believe to be a simple, commonly-used treatment (prefabricated foot orthoses) with some evidence to support it, albeit it relatively low quality (case series evidence) [35]. This change in protocol unavoidably reduces the methodological rigour of the trial, but also increases its external validity.

Secondly, due to the nature of the interventions, research staff cannot be blinded to group allocation. However, follow-up assessment of outcome measures will be via self-completion questionnaires returned by mail, and research staff entering the data and conducting the analyses will be blinded to group allocation. Blinding participants in relation to the two treatments being offered was considered (i.e. by referring to them as “two footwear-related interventions” rather than specifying the rocker-soled shoes and foot orthoses). However, the inherent risk of this approach is that some participants may not be prepared to the wear the rocker-soled shoes for aesthetic reasons (and some could withdraw from the study immediately after being randomised for this reason). On balance, we considered that the reduction in methodological rigour created by poor adherence and differential drop-out was probably greater than that created by lack of blinding; hence our decision to openly advise participants as to the two treatments being compared.

A third, related issue is that because we will openly disclose the two treatments during the recruitment process, there is some risk of “resentful demoralisation” in participants who are allocated to the prefabricated foot orthoses group. That is, some participants who are allocated to receive the prefabricated foot orthoses may be resentful of not receiving the more expensive and (more visually substantial) rocker-soled shoe intervention, which may affect their adherence to the tasks required of them in the study and systematically influence their responses to the outcome measure questionnaires [58]. To address this, we will document both participant preference prior to randomisation and participants’ perceptions of treatment credibility/expectation after randomisation. This approach will not *prevent* resentful demoralisation, but will enable post-randomisation effects of treatment preference to be quantified, and if necessary, factored into the analysis as a prognostic variable.

